### Incidence of adverse events

Adverse events are undesirable and unintentional signs, symptoms, or diseases that appear during or after treatment in a clinical trial. The subjects in the current study will be requested to voluntarily report any adverse events. All adverse events that occur during the trial will be documented. Adverse events that may occur in this study include skin irritation, bleeding, local hematoma, pallor, sweating or dizziness, fainting during acupuncture treatment, retained needle after treatment, continuous severe pain > 1 h after acupuncture, and objective worsening of existing symptoms. The CRC will record adverse events in detail, including the time and date of occurrence, degree of severity, any measurement related to the treatment of the event, and any potentially causal relationship between the treatment and the event, and will report all adverse events to the principal investigator (PI) and the relevant IRB. If serious adverse events occur, defined as those causing severe disability or malfunction, then appropriate measures will be taken and incidents will be immediately reported to the PI and the relevant IRB. If there is an adverse event due to the clinical trial, participants will notify the CRC and the PI, and the participants will be compensated by the “Clinical Trial Compensation.”

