### Participant recruitment

Participants will be recruited at three hospitals in the Republic of Korea, DongShin University Gwangju Oriental Hospital, DongShin University Mokpo Oriental Hospital, and KyungHee Korean Medicine Hospital. The study will be publicized via local newspapers, the Internet, and posters in communities and hospitals. Participants will be given an explanation of the study by the Clinical Research Coordinator (CRC), and will voluntarily sign a form consenting to participation. The CRC will continuously monitor the medical conditions of enrolled participants to maximize adherence to intervention protocols.

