## Discussion

Nearly all ankle sprains are simple grade-I (mechanically stable) or grade-II (some joint laxity) ligament sprains. Grade-III sprains (clinical and/or radiological evidence of instability) constitute a small minority [8]. Although the prevalence of grade-III sprains is low, there is strong evidence supporting the use of immobilization and, occasionally, surgical correction in the management of these injuries [31]. Conversely, clinical standards for the acute management of grade-I and -II ankle sprains are not well defined and there is no evidence supporting a clinically important improvement in outcome with the addition of supervised physiotherapy to usual care in grade-I and -II ankle sprains [32]. KT is one of the functional treatment options for ankle sprain in TKM, which include tape, a semi-rigid brace, and a lace-up brace. “Meridian muscle” is a TKM concept that includes the muscles, ligaments, and tendons of the part where 12 meridians pass. Ankle meridian tendino-musculature and the figure-of-eight shape form of KT treatment is a KT technique applied to the ankle and surrounding meridian muscle, including from ST42 to ST36 over the tibialis anterior muscle to assist active dorsiflexion and inversion, and from GB42 to GB34 over the peroneus longus and brevis muscles to assist active ankle eversion [22].

The objective of the proposed study is to investigate the potentially synergistic effects of KT combined with acupuncture in grade-I and -II ankle sprains, but notably, the study has some limitations. First, there is concern that the short treatment period planned to minimize dropout rates may affect the results of the study. Second, we have no choice but to adopt a single-blinding (outcome-assessor-blinding) approach, because sham treatment is impossible due to the characteristics of the KT method. Efforts to maintain objectivity include separating the CRC who manages the treatment schedules, the practitioner who conducts the treatments, and the assessor.

The results of this study will provide preliminary evidence on the utility and acceptability of KT for patients with grade-I and -II ankle sprains, and will serve as a basis for further research.

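### The stated definition of a serious adverse event is limited to severe disability or malfunction, so a death, life-threatening event or admission without it escapes the immediate-reporting rule

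*Protocol article*

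**What the plan says.** All the rules on this point stand in the protocol article under Incidence of adverse events.

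- **Serious class:** "If serious adverse events occur, defined as those causing severe disability or malfunction".
- **What that class triggers:** appropriate measures are taken, and "incidents will be immediately reported to the PI and the relevant IRB".
- **General rule:** the clinical research coordinator (CRC) records the timing, severity, treatment and possible causality of each event and "will report all adverse events to the principal investigator (PI) and the relevant IRB". No time limit is given.
- **Collection:** "The subjects in the current study will be requested to voluntarily report any adverse events".
- **Completeness promised:** "All adverse events that occur during the trial will be documented".
- **Expected events:** the list includes "objective worsening of existing symptoms".

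Two other sections bear on this. Participant recruitment states: "The CRC will continuously monitor the medical conditions of enrolled participants to maximize adherence to intervention protocols". The Discussion says of blinding that "we have no choice but to adopt a single-blinding (outcome-assessor-blinding) approach", so participants and practitioners know the allocation.

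**The concern.** A serious class exists so that certain events are reported faster than the rest. Here speed is the only thing it adds to the reporting route, because every adverse event already goes to the same two recipients. If the boundary of the class is drawn too tightly, the events for which speed matters most can fall on the slow side.

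The boundary is written as a definition, not as an example. This is therefore a stated rule and not detail that a condensed article has left to the full protocol. Under Quality assurance, the Data Monitoring Committee consists of the principal investigator and the CRC. The IRB is thus the only body outside the trial team that the article names as receiving event reports, and prompt notice to it carries some weight.

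The second, smaller concern is how events come to be known at all. The section promises complete documentation but names voluntary self-report as the means of collection. In a trial without participant or practitioner blinding, that can miss events, and it may miss more in one arm than in the other.

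**Working it through.** The article gives no figure on this point, so the main check is to apply its wording to kinds of event.

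**Step 1. Apply the definition literally.**

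| Event | Meets the stated definition? | Goes to PI and IRB? | Immediate? |
|---|---|---|---|
| Severe disability or malfunction | Yes | Yes | Yes |
| Death, without prior severe disability | Not named | Yes, general rule | Not required |
| Life-threatening event with full recovery | Not named | Yes, general rule | Not required |
| Hospital admission without severe disability | Not named | Yes, general rule | Not required |
| Mild local event, such as skin irritation | No | Yes, general rule | Not required |

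The three middle rows are handled in the same way as the last one. The gap lies in the last column only.

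**Step 2. Look for another clause that would close the gap.** The general reporting sentence has no deadline. The CRC's continuous monitoring under Participant recruitment has adherence as its stated purpose and sets no reporting time. Monitoring by the clinical research associate under Quality assurance concerns documents and compliance with the protocol and SOPs. None of these supplies immediacy.

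**Step 3. Set the collection method beside the promise of completeness.** Participants are asked to report voluntarily, yet all events are to be documented. Some listed events, such as fainting during acupuncture or a retained needle, would be seen by staff. An objective worsening of symptoms needs someone to look for it. The section describes no enquiry at sessions or follow-up contacts.

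**Step 4. What voluntary reporting could do to the counts.** The article gives no event rates or reporting probabilities, so everything here is assumed. Let the true risk *p* be equal in both arms, and let *r*₁ (acupuncture) and *r*₂ (AcuKT) be the probabilities that an event is reported. Which arm is given the higher probability is also arbitrary. The observed risk ratio is (*p* × *r*₂)/(*p* × *r*₁) = *r*₂/*r*₁. The expected reported count per arm is 30 × *p* × *r*, with 30 per arm from the article and *p* = 0.20 assumed.

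| *r*₁ | *r*₂ | Observed risk ratio | Expected reports, acupuncture vs AcuKT |
|---|---|---|---|
| 0.9 | 0.9 | 1.00 | 5.4 vs 5.4 |
| 0.7 | 0.9 | 1.29 | 4.2 vs 5.4 |
| 0.5 | 0.9 | 1.80 | 3.0 vs 5.4 |

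The true expected count is 30 × 0.20 = 6.0 per arm. Equal under-reporting lowers both counts and leaves the ratio at 1. Only unequal reporting distorts the comparison, and nothing in the article shows that it will occur.

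**The case against.** **Nothing is lost.** Every adverse event must be documented and passed to the principal investigator and the IRB, with severity and causality recorded. This stands, and it limits the point to speed of notice.

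**Staff would treat a death as serious in any case.** Malfunction is a loose word and could be stretched to cover a death or a threat to life. That is likely in practice, but a reporting rule should not depend on it, and an admission with full recovery is hard to fit in by any stretch.

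**Such events will be rare.** Treatment is five sessions in one week for grade I or II sprains, and patients with serious disease are excluded. This stands and keeps the weight modest, although follow-up contacts run to 26 weeks.

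**The details of asking about events belong in the case report form or SOPs.** This stands in part: a scripted question may exist there. The article nevertheless names voluntary report as the method, which is why the point is kept as secondary.

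**A reader might infer that the arms cannot be compared fairly.** The documents do not support that. The same request is made of both arms, both attend the same number of sessions, and bias would need reporting to differ between them. Nor is a between-arm safety test stated: adverse events are neither a primary nor a secondary outcome, and Statistical analyses does not mention them.

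**A reader might also suppose that daily re-taping means the skin is inspected in the AcuKT arm only.** Under Intervention, the tape is removed and reapplied daily, but the only inspection mentioned is of medical devices. Irritation caused by tape would in any case be a true effect of taping and not a reporting artefact.

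**Conclusion.** The main point holds. On its own wording, the article leaves three kinds of plainly serious event (death, threat to life, and hospital admission, each without severe disability) outside the immediate-reporting rule. The consequence is delay in notice, not loss of the report. This rests on reading the definition as closed, which is how it is phrased.

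The secondary point holds as a risk only. Voluntary reporting in a trial with unblinded participants and practitioners may under-ascertain events and may do so unequally. The direction and size are unknown, and the risk ratios of 1.29 and 1.80 in the working follow from assumed reporting probabilities, not from trial data.

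Neither point affects the sample size, the primary outcome or the efficacy conclusion. The change is worth making because it concerns participant safety and costs little.

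**What to change.** 1. Replace the definition with full seriousness criteria: death, life-threatening events, hospital admission or its prolongation, persistent or significant disability, and other medically important events. Tie the immediate-reporting rule to that list. If the full protocol already has such a list, bring the article's text into line with it.
2. Replace reliance on voluntary report with one standard adverse-event question, worded identically for both arms and asked at each of the five sessions and at the existing follow-up contacts (4, 8, 12 and 26 weeks). Record the answer on the case report form, including when it is no.
3. Since the trial is described as ongoing, check events already recorded against the wider definition.

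The cost is a few sentences of protocol text and one form item, with no extra visits. Slightly more events will be recorded. Under Quality assurance, a protocol revision needs approval from the Ministry of Food and Drug Safety and the IRBs of all three hospitals.

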### Quality assurance

The trial protocol has been reviewed and revised by experts on acupuncture, orthopedics, rehabilitation, statistics, and methodology several times. Before the trial, all staff will be required to attend a series of training sessions. These sessions will ensure that the personnel involved fully understand the trial protocol and standard operating procedures (SOPs) that will be used during the study. The Data Monitoring Committee is composed of the PI and the CRC. Monitoring and auditing of the clinical trial will be conducted by a clinical research associate (CRA). The CRA will verify all documents related to the clinical trial including Case Report Forms (CRFs) and SOPs, and monitor whether the clinical trial is conducted in accordance with the prescribed protocols and SOPs. Monitoring and auditing will be independent of the PI and sponsor. In the event that the protocol described herein is revised, the revisions will be required to be approved by the Ministry of Food and Drug Safety, and the IRBs of DongShin University Gwangju Oriental Hospital, DongShin University Mokpo Oriental Hospital, and KyungHee Korean Medicine Hospital.

### Sample size calculation

The sample size calculation is based on the primary outcome measure, pain, as determined via the VAS. In accordance with a previous study [30], we have established the number of groups at 2, the effect size as 0.906, with a one-sided alpha level of 0.025, and a statistical power of 0.8. Based on these parameters, the required sample size calculated using G*Power is 42 (21 per group). Estimating a maximum dropout rate of 30%, we have determined that a total of 60 participants—30 in each group—will be required.

### Statistical analyses

Baseline characteristics will be described and compared. Continuous data will be presented as means and standard deviations, and compared using the independent *t* test or Wilcoxon’s rank-sum test, while categorical data will be presented as frequencies and percentages and compared using the chi-squared or Fisher’s exact tests. A repeated-measures analysis of covariance (ANCOVA) will be conducted for the VAS of pain and the secondary outcomes (FAOS, edema, and EQ-5D-5 L). Dependent variables will include values measured before intervention, at the completion of intervention, and 4 weeks after the completion of intervention. A *t* test will be conducted to detect differences between therapies, and repeated contrast tests will be conducted to account for time differences in each group. A *p* value of < 0.05 will be considered significant, and participants who drop out of the study will be excluded from the analysis (i.e.*,* a per-protocol analysis will be performed). All statistical analyses will be performed using SPSS version 22.0.

Data from participants who adhere to < 80% of the protocol procedures (i.e., receive fewer than four of the five scheduled treatments) will be excluded. Missing values will be implemented by multiple imputations. In addition, differences between subjects who complete the study and those who drop out will be analyzed statistically to investigate whether any particular factors are significantly associated with dropping out. Interim analyses will not be performed.

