#### Primary outcome

Given that the objective of this study is to investigate the efficacy of KT on pain reduction in patients with ALAS, the primary outcome assessed will be changes in pain as determined via VAS, which is commonly used in clinical trials and other studies to determine primary outcomes. The VAS that will be used in this study is a 10-cm-long straight line marked at each end with labels that anchor the scale [24]. Patients will be asked to place a mark on the line at a point representing the severity of their pain, where the anchors are “no pain” and “pain as bad as it could be.” Scores are recorded in millimeters, thus yielding a total score range of 0–100 mm. The VAS is often treated as an interval-level scale (with equality between intervals) and subjected to arithmetic operations (e.g., calculation of change scores) and parametric statistics [25].

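### The VAS model lists the pre-randomisation score as a dependent value, names no covariate and fixes no decisive contrast or visit, so the 80% power is not tied to the stated analysis

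*Protocol article*

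**What the plan says.** All places are in the protocol article.

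- **Statistical analyses** specifies a repeated-measures ANCOVA for VAS, FAOS, edema and EQ-5D-5L. On the response it says "Dependent variables will include values measured before intervention, at the completion of intervention, and 4 weeks after the completion of intervention". No covariate is named.
- On the between-group t test, the same section has this: "test will be conducted to detect differences between therapies, and repeated contrast tests will be conducted to account for time differences in each group". It gives neither the value (raw score or change) nor the visit for that t test. It also does not say whether the model's group term or its group-by-time term decides.
- **Primary outcome** states that "the primary outcome assessed will be changes in pain as determined via VAS", again without a visit.
- **Sample size calculation** sets "the effect size as 0.906, with a one-sided alpha level of 0.025, and a statistical power of 0.8" and reports that "the required sample size calculated using G*Power is 42 (21 per group"). It uses no correlation and no number of repeated measures.
- **Randomization** and **Intervention** place the baseline measurement before allocation.

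**The concern.** A VAS score taken before allocation cannot carry a treatment effect. As one of three levels of the response, it enters the average on which the group term is built and pulls that term towards zero. Its useful role is as the covariate, where it removes between-patient variation. A model announced as an analysis of covariance, with its most obvious covariate listed as a response and no other named, gives up that gain.

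The section also leaves several candidate tests of the between-group hypothesis: the group main effect, group-by-time, a t test on a post-treatment score and a t test on change. They estimate different quantities, have different power and can disagree on the same data. The 80% in the sample size section belongs to only one kind of test, and the analysis section does not say that this test is the primary one.

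**Working it through.** **Inputs from the protocol article:** standardised effect d = 0.906; one-sided alpha 0.025 (taken as two-sided 0.05); power 0.8; 21 evaluable per arm; a maximum dropout of 30%; 30 randomised per arm.

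**Assumptions, not in the document:** equal SDs at all visits (set to 1), a common correlation ρ between any two visits, and d standardised to the SD of a single VAS score. I show ρ = 0.3, 0.5 and 0.7.

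**1. The plan's own figure.** Two-sample t test, noncentral t with noncentrality d·√(n/2) and 2n − 2 df. With n = 20 power is 0.797 and with n = 21 it is 0.817, so 21 per arm and 42 in total. Then 42/0.70 = 60. The calculation reproduces, as a plain two-group t test.

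**2. Group main effect over three visits, baseline included.**

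- Effect at both post-treatment visits: expected difference (0 + 0.906 + 0.906)/3 = 0.604, two thirds of d.
- Effect at end of treatment only: 0.906/3 = 0.302, one third of d.
- SD of a patient's three-visit mean: √((1 + 2ρ)/3), which is 0.730, 0.816 and 0.894 for ρ = 0.3, 0.5 and 0.7.
- Standardised effect, both visits: 0.604/SD = 0.827, 0.740, 0.675.
- Standardised effect, end of treatment only: 0.302/SD = 0.414, 0.370, 0.338.

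Averaging also lowers the SD, so the standardised effect falls below 0.906 only when (2/3)/√((1 + 2ρ)/3) < 1, that is, when ρ > 1/6. At ρ = 0.2 and 21 per arm, power is still 0.80. With all 30 per arm retained and an effect at both visits, power is 0.88, 0.80 and 0.73 for ρ = 0.3, 0.5 and 0.7.

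**3. Group-by-time on the same three values.** Univariate F with 2 and 80 df; noncentrality (n/2)·Σ(δₜ − δ̄)²/(1 − ρ). With δ = (0, 0.906, 0.906) the sum of squares is 0.604² + 2 × 0.302² = 0.547, so the noncentrality is 10.5 × 0.547/(1 − ρ) = 8.2, 11.5 and 19.2. An effect at end of treatment only gives the same sum of squares and so the same power.

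**4. t test on change from baseline.** The SD of a change is √(2(1 − ρ)), so the standardised effect is 0.906/√(2(1 − ρ)).

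**5. One post-treatment value with baseline as covariate.** Standardised effect 0.906/√(1 − ρ²) = 0.950, 1.046, 1.269; one df fewer. At ρ = 0.1 it is 0.911, with power 0.82.

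**Power at 21 per arm, two-sided 0.05:**

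| Test | ρ = 0.3 | ρ = 0.5 | ρ = 0.7 |
|---|---|---|---|
| Group main effect, effect at both post visits | 0.74 | 0.65 | 0.57 |
| Group main effect, effect at end of treatment only | 0.26 | 0.22 | 0.19 |
| Group-by-time | 0.71 | 0.855 | 0.98 |
| t test on change at one visit | 0.68 | 0.82 | 0.96 |
| t test on one post-treatment value | 0.82 | 0.82 | 0.82 |
| One post-treatment value, baseline as covariate | 0.85 | 0.91 | 0.98 |

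**The case against.** A reader might infer that the plan fails to deliver its 80% power. The document does not support that, for four reasons.

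- It never makes the group main effect decisive. When baseline is a response level, group-by-time is the usual test of treatment. It is not diluted in the same way, and it exceeds 80% from ρ of about 0.45 upward.
- It names a between-therapy t test, which is the test the sample size matches. On a single post-treatment value, that test has 0.82 whatever ρ is.
- No correlation is given, and 30% is a maximum dropout, so 21 per arm is the planned worst case. The main effect loses nothing against 80% at ρ of about 0.2 or less with 21 per arm. It keeps 0.80 at ρ = 0.5 if all 60 stay.
- The figures of 0.19 to 0.26 need an effect that has vanished by week 4, which the document does not state.

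Two further readings go too far. The text does not say that baseline is excluded as a covariate. It names none, and the full protocol or analysis plan may list one. Nor does it put the within-group contrasts into the efficacy decision: the null hypothesis in the Hypothesis section is between groups. Nothing here inflates the type I error of any single test, and the one-sided 0.025 is no mismatch, because it gives the same sample size as two-sided 0.05.

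All of this stands, and it makes the power loss conditional. It does not remove the stated choice to list the pre-randomisation score among the responses, or the failure to say which test, on which value and at which visit, is primary. A fuller document could add a covariate or a visit, but it would have to change the published sentence to take baseline out of the response.

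**Conclusion.** The concern holds in a limited form. The primary analysis is badly fixed: baseline VAS is a dependent value in a model called ANCOVA, no covariate is named, and the decisive contrast and visit are not identified. The 80% power therefore belongs to a plain two-sample t test and not to the repeated-measures model described.

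The size depends on which test is used. For the main effect with 21 per arm and an effect at both post-treatment visits, power is 0.74 to 0.57 over ρ = 0.3 to 0.7. Other readings of the same section run from below 80% to well above it. All of these figures rest on the assumed equal SDs and common correlation. The defect is one of efficiency and ambiguity, not validity, and it should be settled before the data are analysed.

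**What to change.** - Take baseline out of the dependent variables. Model the VAS at end of intervention and at week 4 with group, time, group-by-time and baseline VAS as covariate.
- Name one visit, and make the adjusted between-group difference at that visit, with its 95% CI, the primary result. State that the sample size refers to this comparison.
- Label the repeated contrasts within groups as descriptive only.
- Use the same form for FAOS, edema and EQ-5D-5L, each with its own baseline as covariate.

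Adding centre, sprain grade or days since injury is optional and not part of the error.

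The cost is a change of wording, a mixed-model procedure in the SPSS package already planned, and one degree of freedom for the baseline term. Baseline VAS is already collected, so no new data or patients are needed. At 21 per arm, power at the named visit is about 0.82 or more for ρ of 0.1 upward, so the planned sample size stands.

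### The only stated analysis set is per-protocol: drop-outs and participants with fewer than four sessions are removed, no analysis of all randomised participants is given, and the scope of the multiple imputation is left unclear

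*Protocol article*

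**What the plan says.** Three rules stand in the Statistical analyses section of the protocol article.

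- Drop-outs: "participants who drop out of the study will be excluded from the analysis", explained in the same sentence as meaning that "a per-protocol analysis will be performed".
- Adherence: those who "receive fewer than four of the five scheduled treatments) will be excluded".
- Missing data: "Missing values will be implemented by multiple imputations". The sentence does not say which participants or which values.

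The section also plans a comparison in which "differences between subjects who complete the study and those who drop out will be analyzed statistically", to look for factors associated with dropping out. No intention-to-treat, full or modified analysis set appears anywhere in the article, and no sensitivity analysis in all randomised participants.

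The Sample size calculation section takes "the effect size as 0.906, with a one-sided alpha level of 0.025" and "a statistical power of 0.8", arrives at 21 per group, and raises this to 30 per group for a maximum drop-out of 30%. The Hypothesis section frames the question as superiority of AcuKT over acupuncture alone on VAS pain. The Blinding section acknowledges that participants and practitioners are not blinded and lists attrition among the resulting risks of bias.

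**The concern.** Randomisation protects the comparison only while the groups analysed are the groups that were randomised. Dropping out and attending fewer than four sessions both happen after allocation, are open to influence from pain and tolerance, and can differ between arms whose participants know what they receive. Removing people on those grounds leaves two selected groups. In a superiority trial the difference between them can no longer be attributed to the tape alone.

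Two further points make the rule hard to apply.

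- Dropping out is not tied to a time point. VAS ends 4 weeks after treatment, while EQ-5D-5L and recurrence run to 26 weeks. On one reading, a participant with complete VAS data who is lost between week 4 and week 26 is a drop-out and leaves the VAS analysis.
- The imputation rule is unrestricted in wording, yet it follows a rule that has already removed the main source of missing data. Two analysts could build different datasets from the same text.

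At stake is the primary conclusion on pain.

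**Working it through.** **1. The plan's own figures.** Inputs from Sample size calculation: d = 0.906, one-sided alpha 0.025, power 0.80, 30% drop-out. Two-sample t test, noncentral t with non-centrality d × √(n/2) and 2n − 2 degrees of freedom:

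- n = 20 per group: power 0.797
- n = 21 per group: power 0.817, so 42 in total
- 42 / (1 − 0.30) = 60

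The sample size reproduces. It is built so that 42 remain after 60 × 0.30 = 18 are lost. The allowance is stated for drop-out only; participants who stay in the study but attend fewer than four sessions are a further loss.

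**2. Possible bias from exclusion.** The article gives no drop-out mechanism and no rates by arm, so everything in this step is assumed: no true effect, 30 per arm, and a fraction f lost in an arm according to a latent variable that has correlation r with worse pain. The mean shift among those who remain in that arm is

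bias (SD units) = r × φ(z) / (1 − f), where z is the (1 − f) quantile and φ the density of the standard normal.

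For f = 0.30: z = 0.524, φ(z) = 0.348, φ(z) / 0.70 = 0.497.

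- r = 0.3: 0.3 × 0.497 = 0.15 SD
- r = 0.5: 0.5 × 0.497 = 0.25 SD, which is 0.25 / 0.906 ≈ 27% of the planned effect

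The bias of the comparison is the difference between the shifts in the two arms. Simulated rejection in favour of AcuKT (nominal 2.5%), with 30% lost in each arm:

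| Where loss is pain-related | r | Bias | One-sided error |
|---|---|---|---|
| Neither arm | 0 | none | about 2.5% |
| AcuKT only | 0.3 | 0.15 SD towards AcuKT | about 7% |
| AcuKT only | 0.5 | 0.25 SD towards AcuKT | about 13% |
| Both arms alike | 0.5 | none | about 2.5% |
| Control only | 0.5 | 0.25 SD against AcuKT | about 0.3% |

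With r = 0.5 in both arms but 30% lost in AcuKT and 20% in control, the shifts are 0.248 and 0.5 × 0.280 / 0.80 = 0.175. The net bias is 0.07 SD towards AcuKT and the error a little over 4%.

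**3. Power if everyone is analysed.** Same noncentral t, 30 per arm. Assumption: all 60 are observed, and a fraction of the AcuKT arm gains nothing, so that the average effect is 0.906 × (1 − fraction).

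| Fraction gaining nothing | Average d | Power |
|---|---|---|
| 0% | 0.906 | 0.932 |
| 10% | 0.815 | 0.874 |
| 20% | 0.725 | 0.788 |
| 30% | 0.634 | 0.676 |

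If some VAS values are missing and have to be imputed, power is lower than these figures.

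**The case against.** **The imputation rule can be read coherently.** A reader might infer that the section contradicts itself, because drop-outs cannot be both deleted and imputed. The text does not go that far: imputation could be meant for intermittent gaps, such as a missed visit or a missing questionnaire, in participants who are retained. What stands is that the scope is unstated and has to be reconciled with the exclusion.

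**Deletion of participants lost after week 4 is not stated.** A reader might take it as certain. The repeated-measures analysis is limited to baseline, end of treatment and 4 weeks, and the Discussion links drop-out to the length of the treatment period. The deletion is one reading of an undefined term.

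**The bias need not favour AcuKT.** A reader might infer an inflated false-positive rate from the open-label design and the tape's skin effects. The article gives no rate of skin irritation. It excludes skin disease at the taping site and lays the tape unstretched to avoid skin problems. Leaving because of skin irritation also does not imply worse ankle pain. The direction and size of any bias are unknown, and the mechanism that produces 13% is reversed if the pain-related loss falls on the controls.

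**The completer comparison and safety.** The planned comparison of completers with drop-outs is useful description, but it does not restore the randomised groups. A reader might also infer that adverse events in excluded participants are discarded. The article says that all adverse events will be documented and does not apply the exclusion to them.

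**An unseen analysis plan could add an all-randomised set.** It could, but the article does not leave the matter open: it states the exclusion and names the analysis.

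**Conclusion.** The point holds. The article fixes a per-protocol set as its only analysis set in an unblinded superiority trial, and this covers the primary VAS outcome. It should be changed before analysis.

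Up to 18 of 60 randomised participants may be removed on the plan's own drop-out allowance. The consequence is a risk of bias in either direction: up to 0.25 SD either way in the assumed scenarios, with a one-sided error between about 0.3% and 13% against a nominal 2.5%, and no bias where loss is unrelated to pain or acts alike in both arms. These figures rest on assumed loss at the plan's 30% maximum and assumed correlations of 0.3 to 0.5. They illustrate the risk and do not predict it.

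The sample size arithmetic is correct and is not part of the point. A reader might infer from the 0.932 that analysing everyone is free of cost in power. That holds only if all 60 are observed and the full effect applies; under full dilution the planned 80% is kept to just under 20%, not at 30%. Possible loss of power does not justify a primary comparison open to selection.

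**What to change.** In the Statistical analyses section:

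1. Define the primary VAS analysis as all randomised participants in the arm assigned, whatever the number of sessions received, using every observed VAS value.
2. Delete the sentence that excludes drop-outs.
3. State whose values are imputed. Handle missing VAS either by the multiple imputation already named, done by arm with baseline and all observed VAS in the model, or by a likelihood-based mixed model.
4. Keep the set with at least four of five sessions as a labelled sensitivity analysis. If the term drop-out is still used there or in the completer comparison, tie it to a time point.

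Cost: a wording amendment, which under the Quality assurance section needs approval by the Ministry of Food and Drug Safety and the three review boards, and slightly more analysis work. The effect may be diluted by participants who did not complete treatment, with the loss of power shown above. The team should accept that openly or revisit the sample size if it expects dilution near 30%.
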